### Study sample and recruitment

The participants are employees of given teams or groups in three organizations that had committed themselves to the study by January 2017. The participating organizations were recruited during 2016–2017 by contacting different organizations that employed knowledge employees, such as office employees and experts whose work tasks are cognitively rather than physically demanding. These organizations include two large divisions of one public organization, and two private enterprises in Finland, which were considered four organizations in the stratification. The organizations’ headquarters are located in the metropolitan area, but they all have regional offices in several other parts of Finland. The organizations represent different fields of business and trade, such as planning, consulting, marketing, customer service, administration, and civil service, in the context of the construction industry, transportation, and government. The participating teams of these organizations mainly work in open-plan offices and the teams may be distributed over several urban areas in Finland.

The recruitment of employees began in October 2017, when the participating organizations were asked to share general information to their teams, employees, and supervisors. The researchers participated in the supervisors’ meetings to briefly provide general information and discuss the study. The employees of the teams were separately recruited for each study phase via email. The longitudinal sample design is fixed panel plus new employees, that is, new employees are added to the original sample during the different stages of the study, and in practice, the employees who no longer work in the organization or the participating unit are excluded from the updated participant lists and dropped from the panel. Participants were recruited during the time slots agreed on with their organization. The contact information of all the members of the participating teams was signed over to the research group before the onset of the first phase. To support retention, we provide participants written feedback on all study questionnaires. In addition, supervisors are contacted regularly during the intervention phase to maintain participation rates. However, participants may withdraw from the study for any reason at any time.

#### Baseline survey, interview, and observation recruitment

We recruited the participants for the baseline survey in November 2017 to February 2018 by sending them a personal email invitation to participate in the study, with a link to the study information and baseline survey. We recruited the participants for the interviews and observations (only active groups) by asking baseline survey participants to volunteer for interviews and observations. We selected the participants to contact so that the work tasks and teams of the organizations were equally represented. We contacted them directly by sending an invitation to participate to 1–3 employees in each clustered team who represented different work roles, gender, and number of years working in the organization. We continued to recruit participants until we obtained the required number.

#### Workshop and intervention implementation recruitment

We recruited the workshop participants at the initial stage (active intervention groups) of the intervention from February 2018, through the organizations’ contact persons, who made the practical arrangements and invited the participants. In two organizations, all the employees from the participating teams were invited, but two other organizations decided to invite mainly supervisors and/or active key figures from among team members. We invited the intervention task reminder questionnaire participants at the implementation stage (active groups) of the intervention from the population invited to the baseline survey plus new members of the participating teams (a fixed panel plus new employees longitudinal design). We also invited the supervisor task questionnaire participants during the intervention implementation, from the participating team supervisor lists.

#### End-of-treatment, post-intervention and follow-up recruitment

We recruited the participants for the end-of treatment surveys from the updated participant lists which included all current employees (active and passive groups) in the participating teams of the participating organization. The participants in the post-intervention actions include those of the evaluation workshops; 3–10 employees or supervisors who have actively participated will be invited along with 3–10 key members from human resources, occupational health and safety, and the management units. Other post-intervention actions that may involve the research group include project-related knowledge-sharing actions.

We will recruit the participants for the four- and ten-month follow-up surveys from the updated participant lists (active groups), which includes all the current employees in the participating teams of the participating organizations.

### Inclusion criteria

The participating organizations selected the units, that is, teams or other organizational units (clusters) to be included in the study. The inclusion criteria were: a) units must include knowledge employees, such as office employees and experts whose work tasks are cognitively rather than physically demanding, b) work performance requires learning and updating knowledge and skills, and c) work is highly dependent on information and communication technology. Furthermore, each participating organization was required to offer several units/teams for the study, to enable us to conduct stratified randomization.

### Sample size

We assumed that all employees would meet the inclusion criteria, and that at least 60% of the participants invited to the baseline survey would respond. It was further assumed that the follow-up attrition would be less than 50%. The meaningful significant difference estimation was calculated on the basis of sub-group differences in previously collected unrelated data (*N* = 2154) on cognitively straining working conditions. The sample size estimations were based on the average size of the teams; we could not define a fixed group size as the clusters in this study are real organizational units that vary in size. According to the power analyses, 32 groups with 15 eligible participants in each is the estimated sample size required to achieve a statistical power of 0.95 with an alpha of 0.05, if the ICC (intraclass correlation coefficient) is assumed to be 0.3 (For detailed information on how group size and ICC affect power, see [43]). Thus, to achieve a significance level of 0.05 when requiring 0.95 power, a sample size of *N* = 480 participants (15 per group) is needed to enable finding a significant difference in the primary outcome of the different arms. A follow-up attrition of 50% and a baseline response rate of 60% would require inviting altogether 1600 participants in order to meet the power requirements defined above. If power was set to 0.80, the required sample size would be 330.

### Randomization

Participants were divided into clusters using existing work communities such as teams, or a shared office. We randomized the clusters into treatment (cognitive ergonomics intervention) and active control (recovery support) groups. Within-organization stratification took into account the type of work tasks within a cluster, the number of respondents in the cluster, and the response rate of the cluster of employees in the first survey. In one organization over 50% of the team members were geographically scattered in some clusters (teams); this factor was therefore used as an additional stratification in this organization. The clusters were ordered using the stratification factors, and a computer-generated random number was used to define whether the even- or the odd-numbered clusters were allocated to the treatment. The allocation ratio was thus 1:1, allocation was not concealed. One member of the research group (PT) planned the randomization procedure which was conducted by PT (for three strata) and VK (for one stratum). The principal investigator (VK) informed the organizations of team allocations, and the contact persons in the organizations invited the teams to the intervention workshops.

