### Study design

The study design is a randomized controlled trial (RCT), applying cluster randomization with stratification allocated groups and parallel assignment. Primary stratification was by organization. Each organization’s clusters were randomly assigned to treatment (Cognitive ergonomics intervention, CE) and active control (Recovery support intervention, RS) conditions. There were four measurement points (Fig. 1): Baseline (before the intervention), End-of-treatment (after the intervention), Follow-up at 4 months, and Follow-up at 10 months. Both in the treatment and the active control interventions the stages consisted of two parts: a kick-off workshop and following weekly intervention task reminders (10 for all participants and an additional 3 for supervisors) which were delivered between the Baseline and End-of-treatment measurements points (Tables 1 and 2). Two organizations also provided clusters for a non-randomized passive control group (PC), which received only the baseline and end-of-treatment surveys.

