### Participants

The total sample in the randomized treatment and active control groups consisted of 1271 office employees from 36 clusters, in four strata (organization A: *n* = 657, B: *n* = 216, C1: *n* = 238, and C2: *n* = 160). We also invited 470 participants from two strata where additional clusters were available (B and C1) to the passive non-randomized control group. In the baseline measurement phase, we received a total of 638 valid responses from the treatment and active control groups (organization A: *n* = 240, B: *n* = 144 and C1: *n* = 153 and C2: *n* = 101), corresponding to a response rate of 50.2% (organization A: 36.5%, B: 66.7% and C1: 64.3% and C2: 63.1%). We obtained 289 valid responses from the non-randomized passive group, the response rate thus being 61.5% (organization B: 54.0% and C1: 81.4%).

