### Outcome analyses

The primary outcome variable is Cognitive Strain Prevalence (see Table 2). Descriptive statistics (frequencies, means and SD), the Mann-Whitney U-test, and chi-squared test will be used for baseline, end-of-treatment, and follow-up (4 month and 10 month) data to determine whether participant and group characteristics are comparable in the treatment and active control groups (randomized groups) and the passive control group (non-randomized group). The main longitudinal data analyses will be based on the Linear Mixed Modelling procedure, including incomplete cases in the analysis and assumes that missing data are random. The data are naturally hierarchical and consist of four organizations, organizational units (clusters), and individual respondents. Organization- and individual-level factors (e.g. gender and age) are included in the model, and the main level of the primary analyses will be that of the cluster. Item-level missing or invalid values are expected to be few, due to the computerized response format, and are not replaced.

Furthermore, additional analyses will include the non-randomized passive control group data in the baseline and end-of-treatment phases. Additional primary outcome analyses will also include post-hoc analyses with possible moderators in the model. The moderators will be defined on the basis of the process evaluation analyses.

Secondary outcome analyses will be the same as for primary outcome measure. We will also analyse subjective productivity measures using difference-in-difference regression. Additional post-hoc analyses such as mixed graphical models or trajectory analyses will also reveal, for example, the factors that predict successful change in a group.

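### Clusters were allocated by an odd/even split of an ordered list, but the primary mixed model as described names none of the cluster-level factors that ordered it

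*Protocol article*

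**What the plan says.** Under Study design, "Primary stratification was by organization". Under Participants, the randomized sample "consisted of 1271 office employees from 36 clusters, in four strata". The number of clusters in each organization is not given.

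Under Randomization, "Within-organization stratification took into account the type of work tasks within a cluster, the number of respondents in the cluster, and the response rate" in the first survey. One organization had geographically scattered teams, and "this factor was therefore used as an additional stratification in this organization". The list was sorted on these factors. For the split itself, "a computer-generated random number was used to define whether the even- or the odd-numbered clusters were allocated to the treatment". The order in which the factors were applied is not given. The section reports who carried out the procedure stratum by stratum, so one random start per organization is the natural reading, but it is not stated outright.

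Under Outcome analyses, the main longitudinal analysis is a linear mixed model on data with three levels (organization, cluster, respondent). "Organization- and individual-level factors (e.g. gender and age) are included in the model", and the cluster is called the main level of the primary analyses. No cluster-level covariate is named.

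**The concern.** List neighbours always fall in opposite arms. Within an organization, one arm always holds the earlier member of each neighbouring pair. A model with organization terms and a cluster random effect treats clusters within an organization as if they had been freely randomized. If the ordering factors carry information about the outcome, that assumption is wrong in one of two ways:

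- **Smooth trend along the list.** The design has balanced the factor, but its variance stays in the cluster error. The standard error is too large and the test is conservative.
- **Alternating factor** (for example, sorted by task type and then by size within type, with few clusters per type). The split puts systematically different clusters in the two arms. The standard error is too small and type I error rises.

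At stake are the calibration of the primary test and, in the first case, some power.

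**Working it through.** **The plan's own figures.** Sample size section: 32 × 15 = 480, and 480 / (0.5 × 0.6) = 1600. Both reproduce. No effect size is stated. With ICC 0.3 the design effect is 1 + 14 × 0.3 = 5.2. With 240 per arm, 0.95 power and two-sided alpha 0.05 (sidedness is not stated), the implied effect is (1.960 + 1.645) × √(2 × 5.2 / 240) = 0.75 SD.

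**Assumptions the documents do not supply.** These are the share R² of between-cluster variance explained by the ordering, the shape of the ordering, the clusters per organization, and any effect size other than the implied 0.75 SD.

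**Post-only analysis, smooth ordering.** The 638 baseline responses (Participants) and the planning attrition of 50% give 638 × 0.5 / 36 = 8.9 per cluster. With unit total variance, SE = √[4 × (0.3 × (1 − R²) + 0.7/8.9) / 36]:

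- nothing modelled: 0.205
- factor modelled, R² = 0.3: 0.179
- factor modelled, R² = 0.5: 0.159

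Simulation with an assumed 14/8/8/6 split and an effect of 0.5 SD, for R² 0.3-0.5:

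| Model | Mean SE | True SD of estimate | Type I error | Power |
|---|---|---|---|---|
| Organization only | 0.204-0.205 | 0.180-0.189 | 2.1-3.6% | 65-66% |
| Plus ordering factor | 0.159-0.179 | – | about 5% | 76-86% |

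At R² = 0 the extra term costs 1-2 points of power (0.658 against 0.642).

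A second simulation used 15 per cluster and a split of 18/6/6/6. At the implied 0.75 SD, the organization-only model has power 0.965 (R² 0.25) and 0.976 (R² 0.50), rising to 0.986 and 0.998 with the factor. There the gain is about 2 points.

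**Post-only analysis, alternating ordering.** With 15 per cluster and R² 0.10 / 0.25 / 0.50, type I error of the organization-only model is 0.08 / 0.13 / 0.21 for an 18/6/6/6 split and 0.07 / 0.10 / 0.15 for 10/10/8/8. Adding the factor returns it to about 0.05. If a factor coincides exactly with odd/even position within organizations, covariate adjustment cannot fully repair it.

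**Baseline used.** Take change from baseline with an assumed cluster autocorrelation of 0.8 and within-cluster correlation of 0.6. A stable ordering factor cancels, so R² drops out:

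SE = √[4 × (2 × 0.3 × 0.2 + 2 × (0.7/8.9) × 0.4) / 36] = √[4 × (0.120 + 0.063) / 36] = 0.143.

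Simulation at R² = 0.5 gives mean SE 0.142 against a true SD of 0.143 and type I error 0.051. Power at 0.5 SD is 0.926 without the factor and 0.928 with it. At R² = 0.3 it is 0.920 and 0.917. With baseline as a covariate, type I error is 0.042-0.047 and the gain is at most 1 point. If the factor also predicts change, the shift in power remains at most about 2 points.

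**Number of possible allocations.** One start in each of four organizations gives 2⁴ = 16 allocations. A two-sided test based on the allocation alone could not go below 2/16 = 0.125. If the organization with scattered teams used two lists, there are 2⁵ = 32 and the floor is 2/32 = 0.0625. No such test is planned. The count only shows that inference has to rest on the model.

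**The case against.** The strongest reply is that the planned analysis is longitudinal, with a baseline and three later measurements, and the primary hypothesis is about a decrease. The ordering factors are fixed features of clusters at baseline. A stable effect of theirs on strain is largely removed by baseline, so the sizeable power loss belongs to an analysis the plan does not describe. This stands, and it takes away most of the magnitude. It does not cover factors that predict change, and the article does not spell out the contrast or how baseline enters.

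Second, the covariates are given by example in a condensed article, and a full list may sit in an analysis plan that is not shown. So it cannot be said that the factors will be left out, only that they are not named. The point survives in that form: the article describes three levels, says which levels supply covariates, and passes over the level at which allocation was restricted.

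Third, nothing in the documents links task type, respondent count or response rate to strain. They may have been chosen to balance arm size and participation. This also stands, and it makes the concern conditional.

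A reader might infer that the intervals are definitely too wide, the test conservative and 10-20 points of power lost. The documents do not support that. It would need no use of baseline, a prognostic strength not documented, an effect of 0.5 SD rather than the implied 0.75, and a smooth ordering.

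**Conclusion.** The mismatch between the allocation and the model as described is real, but its consequence is conditional. Mis-calibration arises only if the allocation factors predict the outcome beyond what baseline strain captures. Its direction cannot be determined because the sort order is not stated. The effect on power ranges from about 0-2 points when baseline enters the longitudinal model to about 10-20 points in a post-only analysis at 0.5 SD with R² 0.3-0.5. All of these rest on assumed R², cluster splits and correlations. One random start per organization is itself an inference. The change is worth making because it is nearly free and removes a question about the primary standard error. It is not evidence that the planned test is invalid.

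**What to change.** In the primary mixed model, include task type, number of baseline respondents, baseline response rate and, where it was used, geographic scatter as cluster-level fixed effects, alongside organization. Describe the method as systematic allocation from a random start, giving the sort order and the number of starts. State that inference is model-based.

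The data were already held for randomization, so the cost is a few model terms. With 36 clusters, four organization terms and one arm term, 36 − 4 − 1 = 31 cluster degrees of freedom remain, and the factors would use a few of these. How many depends on the number of task-type categories, which is not given. If the factors turn out not to be prognostic, the loss in the post-only simulation was 1-2 points of power.

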### Participants

The total sample in the randomized treatment and active control groups consisted of 1271 office employees from 36 clusters, in four strata (organization A: *n* = 657, B: *n* = 216, C1: *n* = 238, and C2: *n* = 160). We also invited 470 participants from two strata where additional clusters were available (B and C1) to the passive non-randomized control group. In the baseline measurement phase, we received a total of 638 valid responses from the treatment and active control groups (organization A: *n* = 240, B: *n* = 144 and C1: *n* = 153 and C2: *n* = 101), corresponding to a response rate of 50.2% (organization A: 36.5%, B: 66.7% and C1: 64.3% and C2: 63.1%). We obtained 289 valid responses from the non-randomized passive group, the response rate thus being 61.5% (organization B: 54.0% and C1: 81.4%).

### Materials

The study methods for collecting data were study questionnaires, an interview and observation method, an intervention workshop method, intervention task reminder questionnaires, and an evaluation workshop method, as described below.

#### Study questionnaires

The study consists of four assessment phases and related questionnaires: baseline (BL), end-of-treatment (EOT), follow-up at four months (FU04) and follow-up at ten months (FU10). Table 3 describes the nine questionnaire modules used.

**Table 3 Tab3:** Study questionnaire modules, description of their content and their assessment schedule

Module	Description	BL	EOT	FU04	FU10
Background *	Nine items on the background of the participant, e.g. age, gender, education, and length of employment.	IGs, PC			
Working Conditions	Ten items on working conditions (developed at FIOH), e.g., number of hours, projects and places to work in a typical work week.	IGs			
Performance	Two items from the Health and Work Performance Questionnaire [39, 40].	IGs, PC	IGs, PC	IGs, PC	IGs, PC
Brain Work Profile (BWP)	BWP questionnaire (developed at FIOH) addresses cognitive demands of work with 39 items in 13 categories. The categories include working amidst disruptions and interruptions, as well as linguistic, memory, and multitasking demands, among others. Each item is assessed for both the frequency and the level of strain vs. engagement.	IGs, PC	IGs, PC	IGs, PC	IGs, PC
Knowledge Work Cognitive Failure Scale (KWCFS)	Modified version of the Workplace Cognitive Failure Scale (WCFS, [49]), with some knowledge work specific items added, resulting in 18 items on cognitive failures in knowledge work, with five subscales: Memory, Attention, Multitasking, Instructions, and Interruptions.	IGs, PC	IGs, PC	IGs, PC	IGs, PC
Copenhagen Psychosocial Questionnaire II (COPSOQ-II)	Seven scales with 23 items [41, 42]: Quantitative demands, Cognitive demands, Work-family conflict, Family-work conflict, General health perception, Burnout, and Cognitive stress.	IGs, PC**	IGs, PC**	IGs, PC**	IGs, PC**
Stress and Recovery	Two items assessed on a scale 0 (not problems at all) to 10 (severe problems)	IGs, PC	IGs, PC	IGs, PC	IGs, PC
Actions	Eighteen items that might affect workflow, such as decreasing the level of office noise or reducing the number of meetings, which were assessed to determine whether the action would improve or reduce workflow.	IGs			
Change	Six items assessed for the level of change, one for each treatment and active control intervention theme: Disruptions, Interruptions, Information Overload, Strain, Recovery, and Work/Life Balance.		IGs, PC	IGs, PC	IGs, PC

*BL* baseline, *EOT* end-of-treatment, *FU04* follow-up at four months, *FU10* follow-up at ten months

*IGs* Intervention groups, include both the Cognitive Ergonomics Intervention group (treatment) and the Recovery Support Intervention group (active control), *PC* Passive Control group

* The background module was included in the EOT survey for those participants who were added after the BL or had not responded the BL survey

** PC received only the Work-Family Conflict and Burnout scales from the COPSOQ-II

The questionnaires were conducted via a secure web-based questionnaire service. At the beginning of each questionnaire, the participants received an email invitation with a description of the study and the questionnaire and reasons to participate. They had about three weeks to answer the questionnaire. Those who had not answered the questionnaire received one to two reminders per week.

